### Research ethics approval and data management

This trial has been approved by The Regional Committees on Health Research Ethics (S-20160160) and registered with the Danish Data Protection Agency (17/13640).

Required information on each participant is recorded electronically in a secure REDCap database [19]. The entered data will be stored on a secure server in The Region of Southern Denmark via Odense Patient Data Explorative Network (https://open.rsyd.dk).

### Study setting

This study is a collaboration between three surgical centres: (1) the Department of Plastic Surgery, Odense University Hospital, Denmark, (2) the Department of Plastic Surgery, Lillebaelt Hospital, Vejle, Denmark and (3) the Department of Plastic Surgery, Telemark Hospital, Skien, Norway.

### Eligibility criteria

We will invite women aged over 18 years to participate in the study if they are eligible for direct-to-implant breast reconstruction. Patients are recruited by either a plastic or breast surgeon in the outpatient clinic. Patients are excluded based on the following criteria:
Prior or planned radiation therapy to the breastTobacco usageHypertension treated with more than one drugBreast ptosis > 2 measured by Regnault’s ptosis scale [20]Body Mass Index (BMI) < 22 or > 32Patients having dementia or any psychiatric disorder, making them incapable of providing informed consent or adherence to follow-up and patients unable to communicate in Danish or English

Patients will receive written information, and if needed, each patient is offered a follow-up conversation together with an assessor. Each patient will have time for reflection prior to deciding if she wants to accept or decline to participate in the study. Patients can only be included after written and oral consent to participate in the study.

### Interventions

We plan to include women scheduled for skin-sparing mastectomy as well as nipple-sparing mastectomy. We perform the skin-sparing mastectomy through a periareolar incision. The nipple-sparing mastectomy is performed through an inframammary-crease incision.

For subcutaneous dissection, we use hydro-dissection (1 l NaCl/1 mL epinephrine). When dissecting the gland of the PMM, we use monopolar cautery as we have described previously [7].

### Subpectoral reconstruction

We divide the PMM insertion infero-medially using monopolar cautery. The division will allow for partial muscle coverage of the implant. The inferior part of the implant is covered by an acellular mesodermal matrix (AMM). This matrix is sutured to the edge of the muscle and the inframammary crease.

We have described the reconstructive technique described in an earlier publication [7].

### Prepectoral reconstruction

The technique used has been published in a paper about prepectoral direct-to-implant breast reconstruction in which we use a single sheet of AMM to cover the implant. The technique is similar in this study, apart from the fact that we have chosen to use two sheets of AMM for full implant coverage [21].

## Follow-up and data collection methods

Pre-surgical data will be collected in the outpatient clinic the day before surgery. Clinical follow-up data will be collected prospectively at 3 and 12 months. We will register all data in a Case Report Form. For registrations of events outside the scheduled follow-up, patients will contact the project responsible person by telephone.

### Outcomes

Before surgery and randomisation, baseline data will be collected in the outpatient clinic. We will record information on age, co-morbidity, medications taken, smoking status, alcohol consumption, whether diabetic, BMI and adjuvant chemotherapy.

The primary outcome measure is the degree of BAD assessed by the NSE scale [15]. Two plastic surgeons will assess the degree of BAD by viewing videos recorded at 12-month follow-up. In cases of disagreement, a consensus is reached. Videos will show each participant in a standing position, relaxed and then performing maximal contraction of the PMM by pressuring the palms of their hands together in the midline in front of their waist. In bilateral cases the most severe side will be used for comparison.

Timeframe: 3 and 12 months.

### Secondary outcome measures

#### Shoulder and arm function

Measurement of the muscular strength of the PMM and deltoids will be examined both before and after surgery. For this purpose, we have chosen the functional assessment tool the ‘Constant Shoulder Score (CSS)’ [22]. This test allows us to make a quantified evaluation of the following four parameters: level of pain, level of function in everyday life, range of movement and strength. We will evaluate the shoulder function bilaterally.

Timeframe: before surgery, and 3 and 12 months after surgery.

#### Quality of life

We will assess the QOL before and after surgery by the reconstructive module of Breast-Q [23].

Timeframe: before surgery, at 3 and 12 months after surgery.

#### Postoperative pain

We will assess the level of pain experienced by the patient at the day of surgery and the three following days by a visual analogue score (VAS) from 0 to 10 where 0 is no pain at all and 10 is worst pain possible.

Timeframe: post surgery and at 3 months after surgery.

#### Length of stay (LOS)

Inpatient days for each patient are recorded as well as days until removal of drains.

Timeframe: number of days until discharge and removal of drains.

#### Duration of surgery

The time of surgery for the two reconstructive methods will be recorded and compared.

#### Complications

We will record any incidence of complications: (1) skin necrosis, (2) wound dehiscence, (3) infection, (4) seroma formation, (5) bleeding and (6) explantation of the implant. Complications will be classified as either major or minor depending on the need for surgical revision in general anaesthesia.

Timeframe: 3 and 12 months after surgery.

#### Aesthetic results

The cosmetic outcome is evaluated by two independent plastic surgeons as well as by the patient [24, 25]. For this purpose, we use a visual analogue scale (VAS) from 0 to 10 were 10 is the best possible outcome.

Timeframe: 3 and 12 months after surgery.

#### Assessment of photographs

Photographs will be evaluated by two independent consultant plastic surgeons and compared to the cosmetic assessment by the patient.

Timeframe: when follow-up is completed.

#### Capsular contracture

The incidence of capsular contracture will be evaluated and classified according to Baker [26].

Timeframe: 12 months after surgery.

#### Surgical corrections

We will record the number of post-reconstructive fat-grafting and surgical corrections within the first year after reconstruction.

Timeframe: 12 months after surgery.

#### New breast cancer and breast cancer recurrence

We will identify the number of new breast cancers developing in the patients who have undergone a prophylactic mastectomy, and the number of breast cancer recurrences in the therapeutically operated patients. We will investigate this 3 years post surgery reviewing the National Patient Register [16].

Timeframe: 3 years after surgery.

### Statistical analysis

We will conduct all our analysis using STATA (StataCorp, College Station, TX, USA). We use baseline variables to describe characteristics of the trial participants. Continuous variables are expressed as mean and standard deviations or as median and interquartile range (25th to 75th percentiles) if the distribution is asymmetrical. Categorical variables are summarised as numbers and percentages. We will compare the categorical variables between groups with a chi-squared test or Fisher’s exact test depending on the number of events. We will compare the continuous variables between groups using an unpaired *t* test or a Mann-Whitney *U* test depending on data representation. A two-sided *p* value of less than 0.05 will be considered significant and reported with a 95% confidence interval. The consistency between different surgeons’ evaluations of BAD and aesthetics will be evaluated using kappa statistics testing the inter- and intrarater reliability [27]. The primary outcome is the proportion of patients with BAD in the subpectorally and prepectorally reconstructed groups. We will compare between groups using the chi-squared test or Fisher’s exact test and a *p* value of less than 0.05 will be considered significant.

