## Methods/design

### Study objectives

The primary outcome of this randomised controlled trial is the degree of BAD, assessed by the NSE scale [15]. The degree of BAD, will be assessed by two plastic surgeons viewing videos recorded at 12-month follow-up. In cases of disagreement, a consensus will be reached.

The primary objective of this study is to compare the degree of BAD between two groups of patients having a direct-to-implant breast reconstruction, randomised to either subpectoral implant placement or prepectoralimplant placement. The secondary objectives and comparisons between groups are: (1) assessment and comparison of the shoulder and arm function by use of the Constant Shoulder Score (CSS), (2) assessment and comparison of quality of life (QOL) by Breast-Q, (3) assessment of postoperative pain by the patients during the first three postoperative days using a visual analogue scale from 0 to 10, (4) comparison of time to discharge, (5) comparison of time for surgery, (6) registration and comparison of complications, major and minor, (7) aesthetic outcome evaluated by two consultant plastic surgeons, (8) assessment and comparison of the degree of capsular contracture and (9) identification of new breast cancer and breast cancer recurrence after 3 years registered in the National Patient Registry [16].

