### Sample size

A non-parametric calculation of the sample size was made based on our assumptions and experience regarding the degree of BAD in the two groups. We used Fisher’s exact test for small sample sizes. Based on our experience we expected that approximately 60% of the patients who are reconstructed using subpectoral implant placement would suffer from BAD as opposed to 20% of the women who are reconstructed using prepectoral implant placement. By using these assumptions in combination with a significance level of 0.05 (one-sided) and a power of 0.95, the total sample size was calculated to 70 patients, 35 women in each group.

However, a retrospective cohort study in women over 18 years of age who had a unilateral or bilateral direct-to-implant breast reconstruction between November 2011 and December 2017 suggested the above sample size assumptions to be too conservative [15]. Therefore, we will conduct an interim analysis with 60% of the patients included (i.e. 0.6 × 70 = 42). The primary hypothesis will be tested conservatively with *n* = 42 patients applying an O’Brien-Fleming type α-spending function (i.e. α_1_^*^ in [18]), resulting in a significance level of 0.0114 at interim and securing an experiment-wise type 1 error of maximal 0.05.

The sample size is calculated using STATA, version 14.0 (StataCorp, College Station, TX, USA) using a two-sample proportion test.

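### CSS and Breast-Q are measured before surgery, but the stated between-group tests do not adjust for that score: valid, but avoidably imprecise on two secondary outcomes

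*Protocol article*

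**What the plan says.** Both scales have a planned pre-surgery measurement. Under Shoulder and arm function the article gives "Timeframe: before surgery, and 3 and 12 months after surgery", and under Quality of life "Timeframe: before surgery, at 3 and 12 months after surgery". Both are between-group objectives; the Study objectives section lists, for instance, "assessment and comparison of the shoulder and arm function by use of the Constant Shoulder Score (CSS").

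The Statistical analysis section has one sentence for every continuous variable: "We will compare the continuous variables between groups using an unpaired" t test or a Mann-Whitney U test, depending on the data. The threshold is two-sided, with a p "value of less than 0.05 will be considered significant and reported with a 95% confidence interval". The only role stated for baseline data is descriptive: "We use baseline variables to describe characteristics of the trial participants". The article mentions no ANCOVA, mixed model, change score or other use of the pre-surgery score in a comparison.

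**The concern.** A patient's pre-surgery score usually predicts part of her later score. A comparison that leaves it out keeps that predictable variation in the error term, although the trial has planned to collect what is needed to remove it.

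The trial is small and was sized for a large difference in BAD only. No power or target difference is stated for CSS or Breast-Q. The Discussion nevertheless gives quality of life the highest importance and suggests that using the pectoralis muscle may impair the shoulder and arm. Wider confidence intervals than necessary on these scales make a real difference easier to miss, and make the similarity of the two methods harder to judge.

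This is a named method, so it is not a detail left to an unseen analysis plan. A plan that used ANCOVA would depart from what the article states.

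**Working it through.** **The plan's own figure.** The Sample size section assumes "approximately 60% of the patients who are reconstructed using subpectoral implant placement would suffer from BAD as opposed to 20% of the women" with prepectoral placement, and reports "a significance level of 0.05 (one-sided) and a power of 0.95, the total sample size was calculated to 70 patients, 35 women in each group". With p1 = 0.6, p2 = 0.2, mean 0.4 and z = 1.645 for both error rates:

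- Uncorrected n per arm = [1.645·√(2·0.4·0.6) + 1.645·√(0.24 + 0.16)]² / 0.4² = [1.645·(0.693 + 0.632)]² / 0.16 ≈ 29.7, so 30.
- With continuity correction: (29.7/4)·[1 + √(1 + 4/(29.7·0.4))]² ≈ 34.5, so 35.
- The exact power of a one-sided Fisher test at 35 per arm is 0.957 (0.949 at 34).

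The 70 therefore reproduces. It concerns the binary primary outcome and does not change under this point.

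**Inputs for CSS and Breast-Q.** 35 per arm and two-sided 0.05 come from the article. The correlation r between the pre-surgery and follow-up score is not given. I assume 0.2 to 0.7, with equal variances at the two times.

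**Formulas.** Relative to a t test on follow-up values (variance 1):

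- ANCOVA: 1 − r²
- t test on change scores: 2(1 − r)
- ANCOVA relative to change scores: (1 − r²)/[2(1 − r)] = (1 + r)/2
- Standard error reduction: 1 − √(variance ratio)
- Number of patients, analysed without adjustment, that 70 adjusted patients are worth: 70/(1 − r²)

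| r | ANCOVA vs follow-up only: variance ratio | SE lower by | 70 patients worth | ANCOVA vs change score: variance ratio | SE lower by |
|---|---|---|---|---|---|
| 0.2 | 0.96 | 2% | 73 | 0.60 | 23% |
| 0.3 | 0.91 | 5% | 77 | 0.65 | 19% |
| 0.5 | 0.75 | 13% | 93 | 0.75 | 13% |
| 0.6 | 0.64 | 20% | 109 | 0.80 | 11% |
| 0.7 | 0.51 | 29% | 137 | 0.85 | 8% |

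**Power, for illustration.** The documents give no target difference. For an assumed true difference of 0.5 SD, I use the noncentral t with noncentrality (0.5/√f)·√(35/2), where f is the relative variance, on 68 degrees of freedom (67 for ANCOVA).

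| r | Follow-up only | Change score | ANCOVA | Difference detectable with 80% power: follow-up only → ANCOVA |
|---|---|---|---|---|
| 0.2 | 0.54 | 0.37 | 0.56 | 0.68 → 0.67 SD |
| 0.3 | 0.54 | 0.41 | 0.58 | 0.68 → 0.65 SD |
| 0.5 | 0.54 | 0.54 | 0.66 | 0.68 → 0.59 SD |
| 0.7 | 0.54 | 0.76 | 0.82 | 0.68 → 0.49 SD |

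**Small-sample check.** Estimating the covariate slope inflates the ANCOVA variance by about 1 + 1/(70 − 4) = 1.015 for a normally distributed covariate. At r = 0.2 the ratio becomes 0.96 × 1.015 ≈ 0.97; at r = 0.7 it becomes 0.51 × 1.015 ≈ 0.52. The tables ignore this factor.

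**The case against.** *The tests are not wrong.* This stands. Under randomisation an unadjusted comparison is unbiased and keeps its type I error. Choosing ANCOVA is a matter of efficiency, and only for secondary outcomes.

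*The rule is generic and may be applied to change scores.* This partly stands. The same sentence covers length of stay and duration of surgery, which have no baseline, and it does not say whether CSS and Breast-Q are tested as follow-up values or as changes. It would go too far to assert that the pre-surgery score will certainly be ignored. Both readings are therefore shown; ANCOVA has the smaller variance in each over the assumed range, though at high r the gain over change scores is modest.

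*The correlation is unknown and may be low.* This stands. Major surgery lies between the measurements, and nothing in the article excludes r = 0.2, where the gain over a follow-up-only test is slight.

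Two stronger readings are tempting. The first is that simple randomisation of 70 patients lets chance baseline differences distort the contrast. The 95% range for such a difference is 1.96·√(2/35) ≈ 0.47 SD, but it carries into the follow-up contrast multiplied by r (about 0.24 SD at r = 0.5), and the unadjusted standard error already includes this variation. It is the same precision loss, not a second problem. The second is that function and quality of life are where 70 patients is most stretched. With no SD, target difference or power given for any secondary outcome, the article cannot support that ranking. Its remark on importance concerns quality of life alone, not shoulder function.

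**Conclusion.** The point holds as a worthwhile, nearly free gain in precision, not as an error. As written, the analysis gives baseline scores no role in the between-group comparison of CSS and Breast-Q. Against a follow-up-only test the gain from adjustment runs from negligible (r = 0.2) to nearly halving the variance (r = 0.7); against a change-score test the order reverses, and the gain is largest at low r.

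That the article states no adjustment is certain. The size of the loss is not: it rests on the assumed r, equal variances at both times, about 35 analysed patients per arm, and a pre-surgery score being available. The power figures rest further on the assumed 0.5 SD.

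**What to change.** In the Statistical analysis section, state that CSS and each Breast-Q scale with a pre-surgery version are compared at 3 and 12 months by a linear model (ANCOVA, or one repeated-measures model) with the patient's own pre-surgery score as covariate. Report the adjusted mean difference with its 95% CI, and keep the Mann-Whitney test as a sensitivity analysis. Scales without a pre-surgery version stay under the present rule.

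For CSS, define one value per patient with its matching baseline. Both shoulders are measured, and a bilateral patient is a single randomised unit, so naming only the operated side would leave bilateral cases undefined. The worst-side rule under Outcomes is given for BAD only. Use the operated side in unilateral cases and, in bilateral cases, one pre-specified summary (for example the mean of both shoulders), computed identically at baseline and follow-up.

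The cost is one degree of freedom and a sentence of text, plus the CSS definition. No new data are needed. The change should be fixed before outcome data are compared by arm.

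### Kappa is specified for surgeons' aesthetic scores recorded on a 0–10 VAS, with no grouping or weights; if it is unweighted, good agreement would be reported as poor

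*Protocol article*

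**What the plan says.** The Statistical analysis section of the protocol article covers rater reliability in one sentence. Its subject is "The consistency between different surgeons’ evaluations of BAD and aesthetics", and it says that the surgeons' "evaluations of BAD and aesthetics will be evaluated using kappa statistics testing the inter- and intrarater reliability". It does not say whether kappa is weighted.

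The two kinds of rating are defined elsewhere in the article:

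- **Aesthetics** (Aesthetic results): "The cosmetic outcome is evaluated by two independent plastic surgeons as well as by the patient", and for this "we use a visual analogue scale (VAS) from 0 to 10 were 10 is the best possible outcome". The recording step is not given. The section Assessment of photographs adds: "Photographs will be evaluated by two independent consultant plastic surgeons and compared to the cosmetic assessment by the patient".
- **BAD** (Outcomes): "Two plastic surgeons will assess the degree of BAD by viewing videos recorded at 12-month follow-up", using the NSE scale. "In cases of disagreement, a consensus is reached". The levels of the NSE scale are not given in the article.

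The Statistical analysis section treats categorical and continuous variables separately when it compares groups: chi-squared or Fisher's exact test for the former, t test or Mann-Whitney for the latter. The reliability sentence makes no such distinction.

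**The concern.** One categorical agreement statistic is assigned to two different kinds of measurement. For a graded or yes/no BAD rating, kappa is a natural choice. For a 0–10 VAS it is not, unless the scale is first cut into categories or the disagreements are weighted by their size, and the article states neither. Unweighted kappa treats scores of 7 and 8 exactly as it treats 2 and 9, and its value depends on how finely the scale is recorded.

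At stake is whether the published reliability figure for the surgeons' cosmetic ratings means anything. The same data could yield a value near zero or one near the ICC, depending on a choice that the text leaves open and that could be made after the ratings are seen.

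A smaller point concerns the word intrarater. Agreement between different surgeons is interrater. Intrarater reliability needs the same surgeon to score the same recording twice, and the article describes no such second reading.

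**Working it through.** The article gives no agreement figure to reproduce, so the check is a simulation of what kappa returns on a 0–10 scale.

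**Inputs from the article:** two surgeon raters; a scale from 0 to 10; 70 patients.

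**Assumed inputs (not in the article):** mean score 7; total SD 1.5, varied from 1.0 to 2.0; true ICC 0.80, 0.90 or 0.95; no systematic difference between raters; scores recorded in steps of 1 or of 0.1.

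**Model.** Each patient has a true score with variance ICC × SD². Each surgeon adds independent error with variance (1 − ICC) × SD². Scores are rounded to the step and limited to 0–10.

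**Formulas.** Unweighted kappa = (p_o − p_e) / (1 − p_e), where p_o is the proportion of exact agreement and p_e the proportion expected by chance. Weighted kappa = 1 − Σw·p_observed / Σw·p_expected, with w the squared difference between the scores (quadratic).

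**Central case, ICC 0.80 and SD 1.5.** The SD of the difference between the two surgeons is 1.5 × √(2 × 0.20) = 0.95 points, so 95% limits of agreement would be about ±1.96 × 0.95 = ±1.9 points. Exact matches are uncommon even though the ranking of patients is well preserved:

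- Whole numbers (70 patients, 400 replicates): exact agreement 0.394, kappa 0.253. The implied chance agreement is (0.394 − 0.253) / (1 − 0.253) = 0.19.
- Tenths: exact agreement 0.051, kappa 0.032. The implied chance agreement is (0.051 − 0.032) / (1 − 0.032) = 0.02.

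A separate run with 200,000 rating pairs gave 0.26 and 0.03, and a quadratic-weighted kappa of 0.77 on whole numbers.

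**Range over SD 1.0 to 2.0 (70 patients, 400 replicates per setting):**

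| True ICC | Step | Unweighted kappa | Quadratic-weighted kappa |
|---|---|---|---|
| 0.80 | 1 | 0.22–0.35 | 0.73–0.77 |
| 0.80 | 0.1 | 0.03–0.05 | 0.79–0.80 |
| 0.90 | 1 | 0.35–0.51 | 0.83–0.87 |
| 0.90 | 0.1 | 0.06–0.07 | 0.89–0.90 |
| 0.95 | 1 | 0.48–0.65 | 0.88–0.92 |
| 0.95 | 0.1 | 0.08–0.10 | 0.95 |

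In every setting the two-way absolute-agreement ICC, estimated from the same data, was within 0.003 of the quadratic-weighted kappa. The shortfall therefore comes from the lack of weights and grows as the scale is recorded more finely. It is not a property of every kappa.

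**BAD.** The Statistical analysis section defines the primary outcome as the proportion of patients with BAD. With two categories, weighted and unweighted kappa are identical, so kappa fits. For the degree of BAD, any loss from not weighting cannot be sized, because the NSE levels are not stated.

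**Repeat reading.** Study objectives, Outcomes, Aesthetic results and Assessment of photographs all describe two surgeons rating. None describes one surgeon rating the same video or photograph twice. Ratings at 3 and 12 months concern different material and cannot supply an intrarater figure.

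**The case against.** The strongest reply is that the article says kappa statistics, a family that includes weighted kappa. With quadratic weights the result matches the ICC almost exactly, so a reader who infers that good agreement will be reported as poor goes further than the text allows. This stands: the understatement is conditional on unweighted kappa. What remains is that the text leaves the choice open for a scale on which the choice decides the answer.

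Second, a reader might infer that the primary outcome is weakened. The documents do not support that. The reliability figure is descriptive, no threshold or decision depends on it, it enters no between-group test, and disagreements on BAD are settled by consensus. Kappa may well suit the NSE grading.

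Third, a reader might infer that the intrarater figure cannot be produced. That is also not supported. BAD is rated from recorded videos and the photographs are assessed once follow-up is complete, so both can be read again. A condensed article may leave the arrangements for a second reading to the full protocol. Only the absence of a description here can be stated.

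Fourth, the mean, SD, ICC and recording step are assumptions, and the values near zero need both unweighted kappa and recording in tenths. This stands for the size of the effect. The direction was the same in every setting tried.

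**Conclusion.** The point holds in a limited form. The article assigns kappa to a 0–10 VAS without categories or weights. If the kappa is unweighted, a true ICC of 0.80 would be reported as about 0.26 on whole numbers or 0.03 on tenths (assumed mean 7, SD 1.5), against about 0.77 to 0.80 with quadratic weights. The consequence is a misleading descriptive reliability figure for one secondary outcome. The comparison of prepectoral with subpectoral placement, for BAD or for aesthetics, does not change. On intrarater reliability, the only conclusion the article supports is a request to confirm that a second reading is planned.

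**What to change.** In the Statistical analysis section:

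1. For the aesthetic VAS, replace kappa with the ICC (two-way, absolute agreement) with its 95% CI, and report limits of agreement between the two surgeons.
2. For BAD, keep kappa, weighted if the NSE grades are ordinal with the weights named in advance, and state that it is calculated on the two surgeons' separate ratings before consensus. Ratings taken after consensus would show agreement by construction.
3. Keep the word intrarater only if the full protocol provides for the same surgeon to re-read the same videos or photographs. Otherwise delete it.

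The first two changes cost a sentence of text and a different Stata command, provided that the separate pre-consensus ratings are recorded. The third costs nothing if the word is deleted or a second reading is already planned. If intrarater reliability is wanted and no reading is planned, it costs a short second viewing of a subset by the same surgeons.
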